#### Secondary outcomes

Participation at 12 months: participation score at 12 months after discharged home (SIS). Quality of life at 6 and 12 months: scores of the other dimensions of the SIS at 6 and 12 months: force dimension, manual function, activities of daily living/instrumental activities of daily living (ADL/IADL), mobility, communication, emotions, memory/thinking, as well as global recovery.

Anxiety and depression scores: change of anxiety and depression scores between discharge home and 6 months, and discharge home and 12 months, measured by the Hospital Anxiety and Depression Scale (HADS) score [31]. Fatigue, sleep quality, and sleepiness: changes in fatigue level measured by the Pichot scale [32], sleep quality measured by the Pittsburgh scale, and sleepiness level measured by the Epworth scale between discharge home and 6 months, and discharge home and 12 months. Epworth scale licence will be obtained before the first inclusion.

Prognosis at 12 months after discharge home: stroke recurrence within 12 months, reported by the patient and/or caregiver and validated by checking the hospital discharge report; unscheduled hospitalisations or emergency room visits within 12 months of discharge from hospital to home reported by the patient and/or caregiver and validated by checking the hospital discharge report; m-RS at 12 months; death at 12 months reported by the caregiver; cognitive disorders at discharge to home and at 12 months, measured by the Montreal Cognitive Assessment (MOCA) scale [33, 34].

Prevention of cardiovascular risk factors: last known blood pressure, LDLc, and glycaemia values, as well as smoking status, physical activity, and body mass index at baseline, 6, and 12 months; these data will be collected by interviewing the patient or in the electronic medical record.

Access to care and social services at 12 months: consumption of care (consultations and hospitalisations) and perceived social aids; these data will be collected by interviewing the patient.

Maintain of the hospital discharge prescriptions at 6 and 12 months (persistence): 6 and 12 months maintenance of secondary treatments for stroke prescribed at discharge, and reasons for discontinuation if applicable; these data will be collected by interviewing the patient and a copy of medical prescriptions will be collected.

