### Measurement of caregiver outcomes

Quality of life: change of the quality of life between discharge home and 6 months, and discharge home and 12 months, measured by Short Form-12 at discharged from hospital to home, 6 and 12 months [37].

Burden: change in burden measured by the Zarit burden scale at 6 and 12 months [38]. Zarit burden inventory licence will be obtained before the first inclusion.

Anxiety and depression scores: change in anxiety and depression scores between discharge home and 6 months, and discharge home and 12 months, measured by the HADS score.

Occupational status: change in professional activity since the patient’s return home (cessation of all professional activity, reduction in working time) in relation to the caregiving situation. Decrease in social and leisure activities since the patient’s return home in relation to the caregiving situation. Satisfaction with the support received upon return home and with information received, measured at 12 months by an ad-hoc questionnair

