### Statistical analysis

Categorical variables will be presented using numbers and percentages, and quantitative variables using mean and standard deviation or median and interquartile range according to their distribution.

Group difference in the SIS Participation domain score at 6 months after hospital discharge will be analysed using a linear model adjusted on the stratification factors (centre and presence or caregiver). The primary analysis will be performed in accordance with the intention-to-treat principle (an imputation method for missing data will be used when appropriate). In a modified intention-to-treat analysis and per-protocol analysis, patients who died before 6 months or those with stroke recurrence before 6 months will be excluded. Change in the SIS participation domain score between 6 and 12 month after discharge will be compared between groups using linear mixed effects model. The model will include patients as random effect, time (6 and 12 months), group (TAU or intervention) and an interaction effect of treatment group × time as fixed effects after controlling for the stratification factors.

Continuous secondary outcomes will be assessed in a similar way. Categorical data will be analysed using logistic or survival models. For non-repeated continuous and binary measurements, ordinary linear regression and logistic or Cox proportional-hazards models will be used when appropriate.

A detailed statistical analysis plan will be made prior to database lock. Analysis and reporting of the results will follow the CONSORT guidelines for reporting randomised controlled trials [45]. Analyses will be conducted using SAS software (version 9.4; SAS Institute Inc., Cary, NC, US). All tests will be two-sided and carried out at the 5% level of significance.

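### 12-month SIS participation is defined as a score at 12 months, but the only comparison named for it is the 6-to-12-month change, which a benefit reached by 6 months and maintained leaves at zero

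*Protocol article*

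**What the plan says.** All references are to the protocol article.

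- **Outcome.** Secondary outcomes defines a level: "Participation at 12 months: participation score at 12 months after discharged home (SIS". Table 2 also lists participation at 12 months as a secondary outcome.
- **Analysis.** Statistical analysis states: "Change in the SIS participation domain score between 6 and 12 month after discharge will be compared between groups using linear mixed effects model". The terms follow: "The model will include patients as random effect, time (6 and 12 months), group (TAU or intervention) and an interaction effect of treatment group × time", with control for the stratification factors.
- **Carry-over.** The next paragraph adds: "Continuous secondary outcomes will be assessed in a similar way". It does not restate time points or contrasts.
- **Exception.** Single measurements are handled separately: "For non-repeated continuous and binary measurements, ordinary linear regression and logistic or Cox proportional-hazards models will be used when appropriate".
- **Other repeated outcomes.** The remaining SIS domains are levels: "scores of the other dimensions of the SIS at 6 and 12 months". HADS is a change from discharge: "change of anxiety and depression scores between discharge home and 6 months, and discharge home and 12 months". Fatigue, sleep and caregiver SF-12 are defined in the same way as HADS, and Table 2 schedules a 1-week value for all of them.

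The primary analysis is separate: a linear model for the group difference at 6 months.

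**The concern.** The score at 12 months and the change from 6 to 12 months answer different questions. The first asks whether the groups differ when the 12-month programme ends. The second asks whether the effect grew or shrank after month 6. The plan defines the first and names the second as its comparison.

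This is more than detail left to a later analysis plan, because the article positively names the quantity to be compared. An analysis plan that follows Statistical analysis inherits the mismatch. One that follows Secondary outcomes departs from the published analysis. Leaving both open until the data are seen would allow a choice between two contrasts, each tested at 5%. The most desirable result, a benefit reached by month 6 and held, is the one the named test cannot show.

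**Working it through.** **Inputs from Sample size:** difference 15 points, SD 27, two-sided alpha 0.05, power 90%, 70 per group, 20% attrition, 170 recruited. **Assumptions:** SD 27 and 68 to 70 evaluable per arm also hold at 12 months; the correlation ρ between the 6- and 12-month scores, which the article does not give, is varied from 0.3 to 0.8.

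**1. The plan's own figure.** n per group = 2(1.960 + 1.282)² × 27²/15² = 68.1, rounded up to 69. A non-central t calculation gives power 0.8997 at 69 and 0.904 at 70, so 70 per group reproduces. With 170 recruited, 170 × 0.8 = 136 remain, or 68 per group, with power 0.895.

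**2. What the model's terms mean.** Let G = 1 for intervention and T = 1 at 12 months, with coefficients β_G, β_T and β_GT.

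- Group difference at 6 months: d6 = β_G
- Group difference at 12 months: d12 = β_G + β_GT
- Group difference in 6-to-12-month change: d12 − d6 = β_GT

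The named comparison is β_GT. The defined outcome needs β_G + β_GT.

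**3. Standard errors, n per arm.**

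- 12-month difference: 27 × √(2/n). At n = 70 this is 4.56.
- Difference in change: SD of change × √(2/n), where SD of change = 27 × √(2(1 − ρ)) = 31.9, 27.0, 20.9 and 17.1 for ρ = 0.3, 0.5, 0.7 and 0.8.

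**4. Sustained benefit.** With d6 = d12 = 15, d12 − d6 = 0. The non-centrality is zero for every ρ, so the named test rejects at its alpha of 5%. For the 12-month difference, 15/4.56 = 3.29, and power = Φ(3.29 − 1.96) = 0.91 by normal approximation (0.904 by non-central t; 0.895 at 68 per arm). Simulation with 20,000 runs at 70 per arm gave rejection rates of 0.052 (ρ = 0.5) and 0.049 (ρ = 0.7) for the change, and 0.902 and 0.906 for the 12-month difference.

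**5. Other patterns** (70 per arm, normal approximation):

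| Benefit at 6 → 12 months | d12 − d6 | Named test rejects, ρ = 0.3 / 0.5 / 0.7 / 0.8 | 12-month difference rejects |
|---|---|---|---|
| 15 → 15 | 0 | 0.05 / 0.05 / 0.05 / 0.05 | 0.908 |
| 15 → 20 | 5 | 0.153 / 0.195 / 0.293 / 0.410 | 0.992 |
| 15 → 10 | −5 | 0.153 / 0.195 / 0.293 / 0.410 | 0.591 |
| 15 → 0 | −15 | 0.793 / 0.908 / 0.989 / 0.999 | 0.05 |

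**6. Outcomes defined from discharge.** If the 1-week value enters as a time point and the groups do not differ there, a 15-point difference in change to 12 months has power 0.793 to 0.999 over the same ρ. This is illustrative, on the SIS planning SD, since the article gives no SDs for the other scales. A sustained effect is then visible. If the model is confined to 6 and 12 months, it does not estimate change from discharge at all.

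**The case against.** The strongest reply is that the model is sound and already contains the 12-month difference, that the 6-month difference is tested separately as the primary analysis, and that a detailed analysis plan is promised before database lock. A sustained benefit would then appear as a 6-month difference with no detected change afterwards. This stands as far as it goes: the fault lies in the named comparison, not in the model. It does not remove the mismatch, because failing to detect a change is not a test of the difference at 12 months.

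A reader might infer more than the article supports:

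- **That the trial would report no difference for a maintained effect.** This is true of the named test only, for the reasons just given.
- **That every continuous secondary outcome is affected.** Non-repeated measures go to ordinary regression. HADS, fatigue, sleep and caregiver SF-12 have a 1-week value that a similar model may include. For these the finding is ambiguity, not certain failure.
- **That the test could wrongly count against the programme.** When a benefit falls from 15 points to 0, a significant interaction correctly detects a real loss of effect.
- **That caregiver burden is mis-analysed.** The definition reads "change in burden measured by the Zarit burden scale at 6 and 12 months", and Table 2 schedules it only at those times. Wording and a 6-to-12-month comparison can agree, so preferring levels is an endpoint preference.
- **That the early value can simply be a baseline covariate.** Randomization is before discharge, the first outcome call is within a week after it, support starts on returning home, and the trial is open. The 1-week value may already reflect allocation, and adjusting for it could remove part of the effect.

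**Conclusion.** The point holds for 12-month SIS participation: the defined outcome and the only named comparison are different quantities. Under a fully sustained 15-point benefit the named test rejects 5% of the time, against about 90% for the 12-month difference. The 5% does not depend on ρ, the SD or the number followed. The 90% assumes SD 27 and 68 to 70 per arm at 12 months. The figures for the change test under growing or fading effects depend on the assumed ρ.

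By the carry-over sentence, the mismatch extends most clearly to the other SIS dimensions. For outcomes defined as change from discharge, the carry-over wording needs clarifying. Because the 6-month primary analysis and the sample size are untouched, this is something that should be fixed rather than a defect that threatens the main result.

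**What to change.** Keep the mixed model and change the statement of what is tested.

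1. For 12-month participation, name the adjusted between-group difference at 12 months as the tested quantity. Report group × time as supportive evidence on durability.
2. For the other SIS dimensions, name the adjusted between-group differences at 6 and at 12 months.
3. For HADS, fatigue, sleep and caregiver SF-12, state that the model includes the discharge/1-week time point and name the contrasts in change to 6 and to 12 months. Note that the 1-week value is collected after randomisation, so these contrasts omit any effect already present by then.
4. Replace the carry-over sentence with a short list giving time points and target contrast for each repeated continuous outcome.

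The cost is one paragraph in the protocol or analysis plan before database lock, with no new data and the same type of model.

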### Qualitative study

During the 12-month visit, clinical research assistants will propose to a sample of patients and their informal caregiver from the intervention group to participate in individual semi-structured interviews. These interviews will help better understanding the processes of effect of the intervention and the strengths and limitations of the transition programme. The interviews will take place preferentially at the individuals’ homes, with the patient alone and with the caregiver alone. They will be conducted by a social psychologist and based on an interview guide elaborated based on Bandura’s theory [25, 26] and validated by the steering committee. An interview will also be carried out after the last patient’s follow-up with the case manager using a specific interview guide (Additional file 2).

The interviews will be audio-recorded and transcribed for analysis. The analysis will focus on data from verbatim, interview notes, and the case manager’s logbook data. A thematic analysis of the content following the approach proposed by Bardin [46] will be carried out using NVIVO software (Nvivo QSR International). A vertical and transversal analysis will be carried out to categorise the verbatim into themes and sub-themes. The analysis grid will follow the themes of the interview grid, enriched during the analysis of emerging themes and sub-themes. The different data sources (interviews, notes, and logbooks) and populations (patients, caregivers, case managers) will be triangulated. The results will then be combined with the results of the quantitative data and collected to analyse the implementation.

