### Study design

The NAVISTROKE trial is a 2-phase study; the first phase will consist in developing the intervention using a user-centred design approach, and the second phase is an open multicentre parallel-group superiority randomized trial. The study will be conducted in two stroke units in France. For qualitative study, semi-structured interviews will be conducted with patients, caregivers and the case manager: between fifteen and twenty interviews will be planned depending on data saturation. This number is planned based on available literature on data saturation [22, 23], however, if new information emerges from the final interviews, additional interviews will be planned.

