### Intervention

Patients in the intervention group will receive telephone support by a trained case manager (number and frequency of contacts defined according to the patient’s needs) and access to an Internet information platform for a 12-month period after returning home following hospital discharge. The planned intervention is described in Table 1. It aims to improve patients’ ability to manage their situation and meet their needs upon returning home, including identifying and requesting the necessary health or social resources. The detailed intervention content will be codesigned during the first phase of the study, using a “user-centred design” approach [24] including the following steps: identification of end-user needs, prototyping/development of the intervention (case management procedures and platform), iterative improvement, end-users testing (Fig. 2). Four workshops involving end-users of the intervention will be planned. This will ensure that the intervention aligns with the context and integrates both experience from professionals’ skills and practices on the one hand, and patients’ and caregivers’ experiential knowledge on the other hand. The intervention content will be underpinned by the cognitive social theory [25, 26] and based on scientific literature, an overview of existing local organisations and the results from previous studies our team conducted on patient needs following the acute phase [27, 28]. The logic model of the intervention (case management + Internet information platform) making the link with the theory and expected outcomes is presented in Fig. 3. For the user-centred design approach, an advisory committee, composed of patients and caregivers, health professionals, social workers, and public health and social sciences researchers, will be formed. This committee will meet during 4 participatory co-design workshops facilitated by a social science researcher and will all last 2.5-3 hours. Following the grid described in Table 1, the advisory committee will: define the case manager’s profile, and required knowledge and skills; identify the resources and tools to be proposed on the Internet information platform; test the tools and content; refine the programme evaluation criteria; and test and validate the study procedures.

**Table 1 Tab1:** Agenda of the co-design workshops during the user-centred design phase

**Workshop number**	**Topics covered**	**Objectives**	**Content and tools**	**Duration**

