### Data collection

Data will be collected from the stroke unit medical charts by external research assistants (from the public health department). For each patient included in the trial, a case report form will be completed with his/her characteristics (age, sex, medical history, comorbidities, treatment, diagnosis, initial stroke severity as assessed by the National Institutes of Health Stroke Scale (NIHSS) at admission, pre-stroke autonomy as assessed by the pre-stroke m-RS).

Patients will be contacted within one week of discharge to home, as well as 6 months and 12 months thereafter for the collection of outcomes. This will be done by telephone [39] by trained research assistants of the study coordinating centre. Research assistants are experienced in stroke patient follow-up by telephone using the standardised scales used for this study. However, training by a stroke neurologist will be conducted before study implementation to ensure standardisation of data collection. Prior to each call, patients will receive the questionnaires by postal or email (or by hand at discharge) so that they can be read and pre-populate the questionnaires prior to the call. Patients will be given the choice of postal or email at inclusion. The data collected are listed in Table 2.

We will precisely detail support received by patients in the control group to describe the usual practices during the study.

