### End of study visit

The end of the search for patients will take place at the end of the 12-month visit. End-of-study data will be collected by telephone by a clinical research assistant; the data collected is specified above.

For patients participating in the qualitative study, participation in the interview will mark the end of the study.

Given the nature of the intervention and the low risk of serious research-related adverse events, no independent monitoring committee is planned for this study

Only the statistician and the coordinating centre will have access to the final trial dataset.

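### No masking of the telephone outcome callers is described, and the role that collects the 12-month outcomes also invites intervention patients to interview during the same visit

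*Protocol article*

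**What the plan says.** The Study design section states that "the second phase is an open multicentre parallel-group superiority randomized trial". No section describes masking of anyone.

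Under Data collection, outcomes at one week, 6 months and 12 months are taken by telephone "by trained research assistants of the study coordinating centre". Their preparation is described as follows: "training by a stroke neurologist will be conducted before study implementation to ensure standardisation of data collection". Questionnaires reach the patient before each call so that answers can be filled in beforehand.

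For the last contact, End of study visit says: "End-of-study data will be collected by telephone by a clinical research assistant". The Qualitative study section gives the same job title a second task at that contact: "During the 12-month visit, clinical research assistants will propose to a sample of patients and their informal caregiver from the intervention group" to take part in semi-structured interviews. The interviews themselves are done by someone else: "They will be conducted by a social psychologist and based on an interview guide". The intervention also has its own staff: "Patients in the intervention group will receive telephone support by a trained case manager".

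**The concern.** Patients and the case manager cannot be masked in a trial of telephone support and a website. The people who telephone for outcomes can be, because they do not deliver the programme. The plan makes no such provision, and at 12 months it works against it, since an invitation limited to the intervention group cannot be made without knowing the group.

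At stake are the outcomes taken at that contact. The m-RS is a judgement by the rater and the MoCA is administered and scored by the rater, so both are open to influence from knowledge of the arm. The 12-month SIS is self-reported but taken in a call. Any such influence adds to the patient-report bias that an open trial already carries, and it is the part that can be avoided.

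**Working it through.** The question is mainly procedural, so the check is to set the sections side by side.

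1. **Who calls.** Data collection names research assistants of the coordinating centre for all three contacts. End of study visit names a clinical research assistant for the 12-month data.
2. **Who invites.** Qualitative study names clinical research assistants, during the 12-month visit, for intervention patients and caregivers only. Steps 1 and 2 give one role both tasks at one contact.
3. **In what order.** Not stated. If the invitation came last and allocation was seen only then, the 12-month scores would be protected. Nothing in the text secures this.
4. **What is exposed, by contact** (study schedule table and outcome sections):

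| Contact | Scales at issue | Items that may hint at the arm | Task that requires the arm |
|---|---|---|---|
| 6 months | SIS (participation is primary) | feeling informed; care use | none |
| 12 months | SIS, m-RS, MoCA | feeling informed; care use; satisfaction | interview invitation |

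The step that requires the arm is therefore at 12 months only, after that patient's primary outcome has been taken.

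5. **Whether other roles exist.** The case manager delivers the programme and the social psychologist interviews. The callers need not do either job, so masking them calls for no new post.

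6. **Sample size.** The plan's figure is 70 per group (difference 15, SD 27, power 90%, two-sided 5%). By the normal formula, n = 2 × (1.960 + 1.282)² × 27² / 15² = 2 × 10.51 × 3.24 = 68.1, so 69. The t-test solution is 69.06, so 70. The figure reproduces, and masking callers does not change it.

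7. **Illustration only.** With 70 per group the standard error of a difference in SIS participation is 27 × √(2/70) = 4.56 points. With no true effect and an assumed interviewer shift of b points, the two-sided false-positive rate is Φ(b/4.56 − 1.96) + Φ(−b/4.56 − 1.96). For b = 2, 3, 5 and 7.5 this gives about 7%, 10%, 20% and 38%. Every b is an assumption and none comes from the documents. The figures show how sensitive the test is to a shift, not that this design produces one.

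**The case against.** The strongest objection is that an article condenses a fuller protocol, that an open trial can still have masked assessors, and that no sentence says the callers are unmasked. This stands as far as wording goes: the accurate statement is that caller masking is not described. It does not dispose of the point, because the invitation is a stated procedure, not a gap. As written, it brings allocation into the 12-month outcome contact.

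A reader might infer that the invitation compromises the primary result, with a false-positive rate of 10% to 20%. The documents do not support that:

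- The primary score is taken at 6 months, before that patient could be invited. Inviting one patient does not reveal another patient's arm.
- Satisfaction is asked only at 12 months, so it cannot unmask the 6-month call. The collector of the details on support received by control patients is not named.
- Filling in questionnaires beforehand leaves the caller less room to shift SIS answers. It gives no evident protection to the m-RS or MoCA.
- The 10% and 20% rates rest on shifts of 3 and 5 points chosen for illustration.

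A reader might also infer that the caller certainly knows the arm while scoring at 12 months. That depends on the order within the visit, which is not given. Finally, training for standardisation helps consistency between callers, but it is not masking.

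**Conclusion.** The point holds as a cheap improvement. One role both records the 12-month outcomes and makes an invitation restricted to one arm at the same visit, in an open trial with no caller masking described. The direct exposure is of secondary outcomes: the 12-month m-RS and MoCA first, then the 12-month SIS. This assumes that the invitation is not held back until outcomes are recorded.

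For the 6-month primary outcome the concern is weaker and rests only on the absence of any masking of the callers. No magnitude can be given for either time point, because the documents offer no basis for the size of interviewer bias.

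**What to change.** - Withhold allocation from the outcome callers in the eCRF at 6 and 12 months. The same software handles randomisation and the eCRF, and access is already restricted. That it can hide the group by role is an assumption to confirm.
- Open each call by asking the patient and caregiver not to reveal their group.
- Take the SIS first (and the m-RS and MoCA at 12 months), before the information, care-use and satisfaction items.
- Have the social psychologist make the interview invitation after the 12-month outcomes are entered. It should not fall to the outcome caller, nor to the case manager, who would be recruiting for interviews that assess the case manager's own programme.
- Record any unmasking, with its timing.

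The cost is an access setting, a call script, a question order and one separate contact for the invitation, all with existing roles. The sample size is unchanged. A later invitation fits the plan, since the interview already marks the end of study for those who take part. Some patients will still disclose their group, and patient-report bias remains.
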